## Abstract

**Background:**

Chronic obstructive pulmonary disease (COPD) has been associated with periodontal disease (PD), and periodontal treatment (PT) has been connected to reduction of lung disease exacerbations. Bronchiectasis has many clinical similarities with COPD but, although it is also a chronic lung disease, to date it has not been studied with relation to PD. The aim of this study is to evaluate whether PT associated with photodynamic therapy (PDT) reduces the number of exacerbations, improves pulmonary function, periodontal clinical parameters and quality of life after 1 year of periodontal treatment follow-up.

**Methods:**

Bronchiectasis patients will undergo medical anamnesis and periodontal examination. Participants with periodontitis will be divided into two groups and PT will be performed as G1 control group (*n* = 32) – OHO (oral hygiene orientation) + supragingival treatment + simulation of using photodynamic therapy (PDT); G2 experimental (*n* = 32) – scaling and root planing + PDT + OHO. Lung function will be assessed both at baseline and after 1 year by spirometry, exacerbation history will be analyzed through clinical records monitoring. Three instruments for quality of life assessment will also be applied – *Saint George’s Respiratory Questionnaire* and Impact Profile Analysis Oral health (OHIP-14). It is expected that periodontal treatment can improve the analyzed parameters after 1 year.

**Discussion:**

Although only one study evaluates exacerbation in COPD after 1 year of PT, bronchiectasis has not been studied in the dentistry field to date. Trial registration: NCT02514226. Version #1. This study protocol receives grant from FAPESP (São Paulo Research Foundation) #2015/20535-1. First received: July 22, 2015, 1^st^ version. This protocol has been approved by the Research Ethics Committee of Nove de Julho University.

## Background

In recent years, many studies have associated periodontal disease (PD) and pulmonary diseases [1]; they have also connected decreased lung function to loss of periodontal attachment [2]. Chronic obstructive pulmonary disease (COPD) is the most studied lung disease related to PD. The pathophysiological process linking both conditions is the destruction of connective tissue and exacerbated inflammatory reaction with large recruitment of neutrophils [3]. In 1 year, periodontal treatment (PT) was able to reduce annual number of COPD exacerbations from 9 to 4 [4].

Bronchiectasis is also a chronic, irreversible lung disease characterized by permanent bronchi dilation. However, it has not yet been studied in the dental field. It is a condition that causes high morbidity, affecting patients’ quality of life [5]. In Brazil, its prevalence is estimated at 4–18% [6]. Many health professionals are not familiar with its diagnosis and, hence, it is often diagnosed as asthma or COPD due to similarities in clinical manifestations [7], such as cough and sputum production [8]. Bronchiectasis patients suffer with recurrent acute exacerbations, which sometimes require hospitalization, increasing public health expending. These patients exacerbate an average of 6.6 times per year [7] and clinical treatment is based on prevention and control of exacerbation episodes, leading to decreased number of hospitalizations.

The etiology of bronchiectasis is extremely heterogeneous and may involve genetic as well as acquired causes. The pathophysiology of bronchiectasis development involves mucociliary changes that result in bacterial colonization and subsequent chronic inflammation with damage to the bronchi [9]. Periodontal pathogens have been found in infected lung fluid [10–12]. Thus, there is biological plausibility in the assertion that a decrease in oral bacterial load could reduce the number of pulmonary exacerbations [5, 6]. To confirm this data, it is essential to measure PT contribution in improving bronchiectasis patients’ quality of life.

Hence, clinical randomized controlled trials are necessary to test if the reduction in oral infection decreases the number of exacerbations [13]. So, the hypothesis of this study is that periodontal treatment can reduce episodes of bronchiectasis exacerbation and improves bronchiectasis patients’ quality of life after 1 year. Therefore, the aim of this study is to determine if periodontal treatment leads to fewer episodes of bronchiectasis exacerbation and improves bronchiectasis patients’ quality of life after 1 year.

## Methods

A randomized, controlled, 12-month, parallel-group clinical trial, registered at www.clinicaltrial.gov (NCT02514226) will be performed. After verbal and written explanation of the study, patients will sign the Informed Consent Form approved by the Research Ethics Committee (# 1.057.901) Universidade Nove de Julho (UNINOVE). A researcher not involved in the study will enroll patients. Forty patients under medical care at InCor-FMUSP with generalized chronic periodontitis will receive periodontal treatment at Universidade Nove de Julho’s Dental Clinic, from August 2016 to September 2018.

### Sample size calculation

For this study, based on exacerbations of bronchiectasis, we assume that the difference between the groups will be one exacerbation with a standard deviation of 1.4 [14] with an effect size of 1. Thirty-two (32) patients per group will be necessary with a significance level of 5%, a power of 80% in a two-group t-test, using the statistical package Dell Statistica version 12.

### Inclusion and exclusion criteria

Patients ≥35 years, of both genders, clinically stable with more than 10 teeth and chronic moderate periodontal disease, i.e., more than 15% of examined teeth with ≥4 mm probing depth (PD) will be included [8]. Patients will be included if they have bronchiectasis, characterized clinically by chronic sputum production and dilated bronchi, and confirmed by chest computed tomography scan. Severity of bronchiectasis will be assessed according to FACED score [14].

Smokers or former smokers who have quit for less than 5 years will be excluded. Also, pregnant women, patients with other lung diseases, such as cystic fibrosis, COPD and asthma, those who are taking medications that affect periodontal condition (e.g., phenytoin or cyclosporine), patients with decompensated systemic diseases, those who required prophylactic antibiotic therapy before periodontal treatment or those who have undergone periodontal treatment less than 6 months prior will be excluded.

### Anamnesis and physical examination

In the anamnesis, questions will be asked about the patients’ general health. Demographic data (age, gender, marital status, occupation, educational level, living conditions and salary) will be collected, as well as medical history data (main complaint, current state of illness, medical and dental history, and medication use), habits and addictions (smoking, drinking, nutrition and oral hygiene).

On physical examination, clinical periodontal parameters will be collected by a single researcher. The calibration will be performed by a single researcher at six sites per tooth for probing depth (PD) and clinical attachment level (CAL) according to Pinto et al. (2016) [8]. The data will undergo the intraclass correlation coefficient test – ICC [15]. Agreement with standard examiner must be >80%.

This researcher will not be involved in the periodontal treatment of bronchiectasis patients. The following periodontal parameters will be evaluated: probing depth (PD), clinical attachment level (CAL), gingival index (GI), visible plaque index, probing bleeding (SS) and suppuration (S) (Ainamo, Bay 1975) [16].

Three questionnaires will be used to assess bronchiectasis patients’ quality of life: *Saint George’s Respiratory Questionnaire – SGRQ,* CoLB, and OHIP-14. They will be applied at baseline and after 12 months after periodontal treatment (Fig. 1).

**Fig. 1 Fig1:**
[figure not shown]
Flow chart summarizing the experimental design

### Analysis of Oral Health Impact Profile (OHIP-14 questionnaire)

The Oral Health Impact Profile (OHIP-14) is a simplified form of the original questionnaire OHIP used for assessment of oral health impact on quality of life [17]. Items are distributed among the following subscales: functional limitation, pain, psychological discomfort, physical disability, psychological disability, social disability, and deficit.

### Saint George’s Respiratory Questionnaire – SGRQ

The specific *Saint George’s Respiratory Questionnaire* (SGRQ) is used to assess quality of life in patients with pulmonary disease [18]. Responses will be evaluated by two experienced physiotherapists ([name] and [name]) that will be calibrated and blinded to perform the evaluation.

### Spirometry

Spirometry tests will be performed by two physiotherapists ([name] and [name]) using ULTIMA CPX *(MedGraphics Corporation®, St. Paul, MN, USA)* with a calibrated pneumotachograph. The technical procedures, acceptance criteria and reproducibility are recommended by the Brazilian Consensus on Spirometry [7]. All patients will perform this procedure after using a bronchodilator (salbutamol 400 μcg inhalation). Variables recorded include FVC (forced vital capacity), FEV1 (forced expiratory volume in one second timed) and FEV1/FVC. The values will be expressed in absolute values and percentage of the predicted for the Brazilian population [12].

### Randomization

Randomization will be performed as described by Pinto et al. (2016) [8] using Microsoft Excel, version 2013. Forty patients will be randomly distributed into experimental and control groups. The randomization will be blocked in groups of four patients.

Opaque envelopes will be identified with sequential numbers and inside of each of them a sheet will be inserted containing the corresponding group information, according to the random order obtained. The envelopes will be sealed and remain sealed in numerical order in a safe place until the time of periodontal treatments.

Patients will be allocated into experimental and control groups as follows:
**Group 1** – control group (*n* = 32) – OHO (oral hygiene orientation) + supragingival treatment + simulation of using photodynamic therapy (PDT)

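### The protocol gives two totals, 40 patients treated and randomised and 32 per group (64); the stated 80% power holds only at 64 and would be about 60% at 40

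*Protocol article*

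**What the plan says.** Only the protocol article is at hand. It gives the size of the trial in several places.

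- **Methods, opening paragraph:** "Forty patients under medical care at InCor-FMUSP with generalized chronic periodontitis will receive periodontal treatment".
- **Randomization:** "Forty patients will be randomly distributed into experimental and control groups", in blocks of four.
- **Sample size calculation:** "Thirty-two (32) patients per group will be necessary with a significance level of 5%, a power of 80% in a two-group t-test". The inputs are given just before: "we assume that the difference between the groups will be one exacerbation with a standard deviation of 1.4", and then "with an effect size of 1".
- **Abstract (Methods) and the group list under Randomization:** n = 32 for the control group and n = 32 for the experimental group.

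The Study variables section names the number of exacerbations as the primary variable, so the calculation concerns the primary comparison. The forty is nowhere described as a per-arm number, a first stage, a subset or a count of completers.

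**The concern.** Two statements put the total at 40. The sample size section, the Abstract and the group list put it at 64. The Randomization section holds both within a few lines: forty patients are shared between two groups, each of which is then listed with 32. If the control group took 32 of the forty, 8 would be left for an experimental group listed with 32.

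The total decides two things. It fixes the length of the Excel list and the number of sealed envelopes. It also decides whether the stated 80% power applies to the primary comparison. If the trial closed at 40 while the protocol still claimed 80%, a null result would be read as stronger evidence against a one-exacerbation difference than the trial could give.

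**Working it through.** **Inputs, from the Sample size calculation section**

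- Difference: 1 exacerbation; SD: 1.4. The standardised difference is d = 1 / 1.4 = 0.714.
- Significance level 5%, power 80%, two-group t-test. The section does not say one-sided or two-sided.
- Required size: 32 per group.

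**Assumption:** equal allocation. No ratio is stated, but it follows naturally from the equal listed arms and the blocks of four. Forty then means 40 / 2 = 20 per group. For a fixed total and a common SD, an equal split gives the most power, so this assumption favours the 40-patient reading.

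**Step 1. Reproduce the plan's figure.**

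Normal approximation, two-sided: n per group = 2 × (1.960 + 0.842)² × (1.4 / 1)² = 2 × 7.85 × 1.96 = 30.8, rounded up to 31.

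Non-central t, two-sided: 31.76, rounded up to **32**. This is the plan's number.

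**Step 2. See whether another reading gives 32, or gives 20.**

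| Reading | n per group for 80% power |
|---|---|
| Two-sided, d = 0.714 | 31 (normal), 32 (t) |
| One-sided, d = 0.714 | 25 |
| Two-sided, standardised d = 1 | 16 (normal), 17 (t) |

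Only the two-sided test with d = 0.714 gives 32, so the effect size of 1 in the text must be the raw difference. No reading gives 20 per group.

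**Step 3. Power at each total, same inputs, two-sided.**

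The non-centrality parameter is d × √(n / 2), with 2n − 2 degrees of freedom.

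- 32 per group: 0.714 × √16 = 2.857, 62 degrees of freedom. Power is 80.3% (normal approximation: Φ(2.857 − 1.960) = 81.5%).
- 20 per group: 0.714 × √10 = 2.259, 38 degrees of freedom. Power is **59.5%** (normal approximation: Φ(2.259 − 1.960) = 61.7%).

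The type II error at 20 per group is 100 − 59.5 = 40.5%, about twice the planned 20%.

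**Step 4. Difference detectable with 80% power at 20 per group.**

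The non-central t gives d = 0.909, and 0.909 × 1.4 = **1.27** exacerbations, against the 1 assumed.

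**Step 5. Can the block size decide between the totals?**

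40 / 4 = 10 blocks and 64 / 4 = 16 blocks. Both are whole numbers, so it cannot.

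**The case against.** The best answer to this point is that 64 is plainly the intended size. It is the only total with a derivation, the derivation is correct, and the Abstract and both arm listings agree with it. The two mentions of forty could be uncorrected remnants. In that case the power is as stated and the defect is one of wording.

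Much of this stands. A reader might infer that the trial will in fact be run at 40 and is therefore underpowered. The document does not support that. The Randomization section, which staff would follow, lists 32 in each arm as well as forty in total, so it cannot show which number would be carried out. The 60% is conditional on 40 being the real number. The objection does not remove the conflict, however: forty appears in two separate sections, once for treatment and once for randomisation, and no text withdraws it.

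A reader might also infer that 64 is itself too few because no allowance for dropout is shown. That is not part of this point. The article gives no expected loss rate, and such an allowance is commonly left to the full protocol or analysis plan.

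Other readings of the calculation do not rescue 40. A one-sided 5% test at 20 per group has 72% power (73% by the normal approximation), still below 80%, and would have required 25 per group. A standardised effect of 1 at 20 per group has 87% power (89% by the normal approximation), but it contradicts the stated SD of 1.4 and would have required 16 or 17 per group. Neither fits the stated 32.

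**Conclusion.** The point holds as an internal contradiction in the total sample size: 40 in the opening of Methods and in the first lines of Randomization, against 32 per group (64) in the Sample size calculation, the Abstract and the group list. The calculation itself is sound, and its 80% belongs to 32 per group only. If 40 are randomised, power for the primary comparison is about 60%, and the difference detectable with 80% power is about 1.27 exacerbations. These figures rest on the protocol's own difference and SD, on a two-sided test (the reading that reproduces 32) and on equal allocation. The conflict should be resolved before the allocation list is made, because the number governs the primary analysis and the document leaves it open.

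**What to change.** Use one number throughout the Abstract, the opening of Methods, the Sample size calculation, and the Randomization section with its group list.

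- **If 64 is intended:** change forty to 64 in the opening of Methods and in Randomization, and prepare the list and envelopes for 64. The power statement stays. The cost is two corrections in the text. If only 40 patients had been planned for in practice, it also means recruiting 64 − 40 = 24 more.
- **If 40 is what will be done:** change n = 32 to n = 20 per arm in the Abstract and the group list. In the Sample size calculation, replace the claim of 32 per group at 80% power with 20 per group, giving about 60% power for a difference of 1 exacerbation and 80% for about 1.27. The cost is a less favourable stated power.

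In either case, state in the Sample size calculation that the test is two-sided and that the 1 is the raw difference, so that the figure can be reproduced without inference.

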### Blinding

Patients of control group will receive simulation of using photodynamic therapy (PDT).

The simulation of PDT will be performed by applying methylene blue (0.005% - Chimiolux 10, DMC® – Purified water and methylene blue) with a carpule syringe and needle (with stop and without bevel) into the periodontal pockets >4 mm. Then, wait for 3 min (Betsy [19]). Irradiation will be performed with the laser (MM Optics Twin Laser, São Paulo, SP, Brazil) turned off in all sites around a tooth (six sites per tooth) on all teeth, lastly, 1 min irradiation scanning around each tooth. Than, the operator will wash abundantly with saline until complete removal of methylene blue.

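### A disclosed, fixed block size of four leaves up to a third of allocations deducible by anyone who has followed the sequence; varied, undisclosed blocks are a cheap improvement

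*Protocol article*

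**What the plan says.** The protocol article, under Randomization, states: "The randomization will be blocked in groups of four patients". It then describes the concealment: "Opaque envelopes will be identified with sequential numbers", each holding a sheet with the group, and "The envelopes will be sealed and remain sealed in numerical order in a safe place until the time of periodontal treatments".

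Under Methods, enrolment is kept apart from the trial team: "A researcher not involved in the study will enroll patients". Patients are treated at one university dental clinic, and no stratification is described. Table 1 places consent and eligibility screening before allocation, and allocation before the interventions.

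The arms are supragingival treatment with simulated photodynamic therapy, or scaling and root planing with active photodynamic therapy. Under Blinding, the simulation is described as follows: "Irradiation will be performed with the laser (MM Optics Twin Laser, São Paulo, SP, Brazil) turned off in all sites around a tooth". That section concerns what control patients receive. It does not say that the operator is blinded.

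**The concern.** Sealed, opaque envelopes hide an allocation from sight but not from deduction. With one clinic, no strata and a constant block of four, blocks end at envelopes 4, 8, 12 and so on. Whoever has seen the earlier allocations and knows the block size can work out the last place in every block, and sometimes the last two. Operators cannot avoid learning each arm, since they do the scaling and switch the laser on or leave it off.

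If such a person could also influence who takes the next envelope, patients could be steered towards one arm. The planned comparison under Statistical analysis is an unadjusted t-test or Mann-Whitney test, which would not correct a resulting imbalance.

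**Working it through.** **Inputs**
- Block size 4, stated under Randomization.
- Ratio within a block: not stated. I assume 2:2, from the equal arms under Sample size calculation ("Thirty-two (32) patients per group will be necessary").
- Number randomised: 40 according to Randomization ("Forty patients will be randomly distributed into experimental and control groups"), or 64 from two arms of 32 elsewhere. These figures conflict, which is a separate matter, so I carry both.
- The article gives no figure for predictability. Its 32 per group does reproduce: a two-sided t-test with difference 1, SD 1.4, 5% significance and 80% power gives 31.76, rounded up to 32. Here it serves only to count patients and, in the last step, to set the standard error.

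**Share of allocations that are certain**
The six equally likely blocks are AABB, ABAB, ABBA, BAAB, BABA and BBAA. An allocation is certain once one arm's two places are used.
- AABB and BBAA: the third and fourth are certain, so 2 each.
- The other four blocks: only the fourth is certain, so 1 each.
- Expected per block: (2 × 2 + 4 × 1)/6 = 4/3. Share: (4/3)/4 = 33.3%.
- 40 × 1/3 = 13.3 patients; 64 × 1/3 = 21.3 patients.

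**Share of best guesses that are correct**
- First place: 1/2.
- Second: guess the opposite arm, right 2/3 of the time.
- Third: certain in 1/3 of blocks, otherwise even, so 1/3 × 1 + 2/3 × 1/2 = 2/3.
- Fourth: 1.
- Total 2.833 of 4 = 70.8%, against 50% without blocking.

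Both shares require knowledge of the block size, the block boundaries and all earlier allocations in order. Without the earlier allocations, the certain share is 0%.

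**Alternatives**
Fixed sizes are enumerated exactly. Mixed sizes are simulated (3,000 lists of 64, sizes equally likely), with an observer who knows the set of sizes but not their order.

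| Block sizes | Certain | Best guess correct |
|---|---|---|
| Fixed 4 | 33.3% | 70.8% |
| Fixed 6 | 25.0% | 68.3% |
| Fixed 8 | 20.0% | 66.6% |
| Random 4, 6 | 5.6% | 69.1% |
| Random 4, 6, 8 | 2.2% | 67.8% |

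With 4, 6 and 8, about 64 × 0.022 = 1.4 allocations are certain. The gain depends on hiding the order of sizes. If that order were known, the certain share would be (4/3 + 6 × 0.25 + 8 × 0.20)/(4 + 6 + 8) = 4.43/18, about 25%.

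**What steering could do (illustration only)**
The article gives no figure for steering. Assume a fully informed person raises the expected exacerbations of patients in certain places by δ for one arm and lowers them by δ for the other, with δ from 0.25 to 0.5.
- Bias = 2 × (1/3) × δ = 0.17 to 0.33 exacerbations, against a planned difference of 1.
- Standard error = 1.4 × √(2/n): 0.35 at 32 per arm, 0.44 at 20 per arm.
- By normal approximation, a two-sided 5% test then rejects a true null about 8% to 16% of the time at 32 per arm, and about 7% to 12% at 20 per arm.
- Someone who acts on every best guess, right with probability p, produces a bias of 2δ(2p − 1). That is 0.83δ with fixed blocks of four and 0.71δ with mixed blocks, so mixing helps much less against this behaviour.

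**The case against.** The strongest reply is that nobody is shown to have both the knowledge and the opportunity. Operators must know the arms, but the article gives them no part in enrolment, scheduling or keeping the envelopes. If there are several operators, each sees only part of the sequence. A person outside the study enrols. All of this stands, and it makes the exposure a residual one.

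A reader might infer that keeping envelopes closed until treatment causes the predictability. It does not. Late opening, after consent and eligibility, is a safeguard. The article says when envelopes are opened, not when a number is tied to a patient, and the separate allocation column in Table 1 fits numbering before treatment.

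It can also be said that who prepares the list, who books visits and when numbers are assigned are details an article may leave to the full protocol, and that the Randomization section refers to a cited study for its procedure. That also stands, so those silences are not errors. The block size is different, because the article states it.

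Finally, the benefit measured by best guesses is only about 3 percentage points (70.8% to 67.8%). That is correct and limits the claim. The large gain is in certain allocations.

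**Conclusion.** The point holds as a cheap improvement. The stated design lets a fully informed observer know 33.3% of allocations in advance (about 13 of 40 or 21 of 64) and guess 70.8% correctly. This rests on 2:2 blocks, on no stratification, and on an observer who knows the block size and the full run of earlier allocations. That operators know each arm is an inference, but an unavoidable one.

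A reader might go further and conclude that a third of allocations are open to everyone, or that selection bias is built in. The documents support neither: the share is zero for anyone without the earlier allocations, and no one who has them is shown to control enrolment or treatment order. Nor do the documents support an argument that a few steered patients matter because the outcome depends strongly on prior exacerbations; the article does not say that it does. The false-positive rates above show what assumed steering would do. They are not a forecast for this trial.

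**What to change.** Replace the fixed block of four with block sizes varied at random, for example 4, 6 and 8. State in the protocol that sizes vary and that neither the sizes nor their order is disclosed to enrolling or treating staff.

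As a supporting step, add a sentence that each patient receives the next envelope number when eligibility is confirmed, so that appointment order cannot affect allocation. The envelopes can stay sealed until treatment as planned. This step matters because varied blocks lower best-guess accuracy only slightly.

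The cost is a new list and a sentence or two, with no extra patients or staff. The downside is a small imbalance if recruitment ends within a block: at most 4 patients with a largest block of 8. At 64 patients the worst split is 34 and 30, and 1/34 + 1/30 = 0.0627 against 2/32 = 0.0625, a variance increase of about 0.4%. At 40 patients, 22 and 18 gives 0.101 against 0.100, about 1%.
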